## Abstract

Rheumatoid arthritis (RA) is a chronic autoimmune disease that primarily affects cartilage and bone. Psychological stress can both trigger disease exacerbation and result from disease activity. As standard pharmacological interventions alone have limited success in treating RA, a more comprehensive biopsychosocial approach to treatment has been recommended. In this prospective randomized controlled trial (RCT), a psychotherapeutically guided, group-based intervention program will be conducted with RA patients over a period of 9 months. This program combines a dynamic-interactional model with disorder-specific coping-oriented perspectives to improve patients’ social, emotional, and problem-solving competencies as well as stress system functional status. The enrolment of 440 patients, randomly allocated to either an intervention (*n* = 220) or control group (*n* = 220), is planned. To evaluate the intervention effect, various indicators of RA disease activity, stress system activity, and psychological condition will be assessed through sets of standardized questionnaires and biochemical analyses of blood and saliva samples. Moreover, healthcare-related costs for each patient will be obtained using routine health insurance data. Outcome variables will be measured in all patients at regular intervals prior to intervention (baseline), during the 9-month intervention (five time points), and during a 9-month follow-up phase (three time points), allowing the comprehensive analysis of within- and between-subject effects, i.e. trajectories of the target variables in the intervention and control groups. In addition, to investigate the intervention effects on real-life stress system functioning in RA, 10 integrative single-case studies (*n* = 5 from the intervention group, *n* = 5 from the control group) will be conducted. In each study, once before and after the 9-month intervention, urine samples will be collected, and patients will fill out questionnaires for approximately 1 month at 12-h intervals. Moreover, weekly in-depth interviews will be conducted with patients to determine their previous week’s emotionally positive and negative incidents. Using time series analysis, it is then possible to investigate whether and how stress system function in these RA patients has improved from the applied intervention. By using both an investigational macro- and microperspective, this project aims to evaluate a psychological intervention in the routine care of individuals with RA.

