Furthermore, weekly in-depth psychological interviews (lasting approximately 1 h) using the Incidents and Hassles Inventory (IHI) will be conducted with the patient via online videoconferences. These interviews aim to identify the previous week's negative and positive emotionally meaningful incidents, which will subsequently be rated by a three-person panel following the study period. Additionally, the patients will have weekly appointments with their rheumatologists to determine their DAS 28 (CRP/ESR), SDAI, and CDAI scores.

Using the integrative single-case design, researchers can construct various equidistant time series from biological, psychological, and social datasets. These time series can be statistically analysed to determine their temporal relationships. For instance, one can investigate whether one variable significantly precedes or follows another [36, 37], identify response patterns between variables [17, 38], and determine the duration of temporal delays between variables [39, 40]. For further details on the study design, see [23].

Before the intervention begins, all ten patients participating in the integrative single-case studies will collect data as previously described for the 3-month period leading up to the intervention. In contrast, the follow-up data collection periods are staggered: two patients will be monitored within 1 to 4 months after the intervention ends, four patients within 5 to 8 months after, and four more patients within 9 to 12 months after, each for approximately 1 month. This design allows for the identification of functional changes before and after the intervention, such as alterations in the patients’ psychophysiological response to emotionally meaningful positive and negative incidents.

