In the statistical analyses of the integrative single-case studies, time series variables will be tested on mutual dependency using autoregressive integrated moving average models (ARIMA), cross-correlational analyses and vector autoregressive models (VAR). First, it will be necessary to consider that each time series––psychosocial or biochemical––is governed by two main factors: an internal dynamic structure, giving rise to serial dependency, and serially uncorrelated disturbances. Because of such serial dependencies, an unadjusted cross-correlational analysis may lead to spurious correlations. Therefore, these dependencies will be separated from the disturbances by applying ARIMA filters to the time series. To determine whether one variable significantly precedes and thus predicts another, cross-correlations with the filtered residuals will be computed, both at lag zero (i.e. contemporaneous correlation) and higher lags (up to ± 14) with a significance level of *p* < 0.05.

All planned analyses will be performed with both the newest version of IBM SPSS Forecasting [42] and statistical software *R* [25] using the packages *lme4* (generalized linear mixed-effects models) [24], *tseries* (basic time-series analysis) [43], *forecast* (ARIMA models) [44], *vars* (VAR models) [45], and *ggplot2* (graphical processing) [46].

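### The single-case studies ask whether stress-system responses changed from before to after the programme, but the stated analysis only tests whether two series are related within one monitoring month

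*Protocol article*

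**What the plan says.** The question is put as a change. The Abstract says the time series analysis makes it possible to investigate "whether and how stress system function in these RA patients has improved from the applied intervention". Under Integrative single-case studies the article says "This design allows for the identification of functional changes before and after the intervention, such as alterations in the patients’ psychophysiological response", meaning the reaction to meaningful incidents. The Discussion again presents this component as showing how an intervention alters the functioning of the stress system.

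The analysis is put as a dependency. Under Statistical analyses, "time series variables will be tested on mutual dependency" with ARIMA models, cross-correlations and VAR models. The series are first filtered by ARIMA. Then comes the only significance criterion for this component. Its aim is given as "To determine whether one variable significantly precedes and thus predicts another". The test that serves this aim is described as follows: "cross-correlations with the filtered residuals will be computed, both at lag zero (i.e. contemporaneous correlation) and higher lags (up to ± 14) with a significance level", which is set at 0.05.

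The design is ten patients, five per arm, each followed for about one month before and one month after the programme, at 12-hour intervals. The second month falls 1–4 months after the programme ends for two patients, 5–8 months for four, and 9–12 months for four. The Background calls the mechanism findings exploratory. Trial status (version 5.0) reports one single-case study conducted and more being sought.

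**The concern.** The null hypothesis of the stated test is that two filtered series are uncorrelated at a given lag within one month. The null hypothesis that matches the question is that the correlation is the same in both months. A test of the first says nothing direct about the second: two estimates can fall on either side of a significance threshold without differing from each other.

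VAR models are named, but with no term for monitoring period, so they do not supply the contrast. No comparison of intervention with control cases is stated either. Yet the Abstract speaks of improvement due to the intervention, and the second month comes long after the first and at staggered distances. A before–after difference in one patient could therefore reflect the passage of time.

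At stake is the stated purpose of this component. Without a test of change, the significance results can describe each month, but they cannot support a statement that a response was gained, lost or altered.

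**Working it through.** The article gives no error rate or power for the before–after comparison, so there is no figure to reproduce. The check asks what would happen if change were read from the stated criterion.

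**Inputs from the article**
- Sampling every 12 hours for about one month: 2 × 30 = 60 points per series (56 to 62 tried as a range).
- Lags from −14 to +14: 2 × 14 + 1 = 29 tests per pair of variables.
- Significance level 0.05; sidedness not stated.

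**Assumptions**
- Two-sided testing.
- Residuals white after filtering.
- The same true cross-correlation r in both months, so nothing has changed. The article gives no value for r; the range 0 to 0.5 is shown.
- A reading rule that the article does not state: significant in one month and not in the other counts as a change.

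**One pre-chosen lag.** The critical value is 1.96/√60 = 0.253. On the Fisher z scale the standard error is 1/√57 = 0.132. With p the chance of significance in one month, the chance that two independent months disagree is 2p(1 − p).

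| True r (both months) | p | 2p(1 − p) |
|---|---|---|
| 0 | 0.051 | 9.7% |
| 0.1 | 0.119 | 21% |
| 0.2 | 0.337 | 45% |
| 0.25 | 0.490 | 50% |
| 0.3 | 0.650 | 46% |
| 0.4 | 0.894 | 19% |
| 0.5 | 0.986 | 2.8% |

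Example, r = 0.25: z(0.253) = 0.259 and z(0.25) = 0.255, so p = 1 − Φ((0.259 − 0.255)/0.132) ≈ 0.49, and 2 × 0.49 × 0.51 = 0.50.

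Simulation with a true lag-1 relation and 60 points gave 9.7%, 44%, 50%, 47%, 20% and 3% at r = 0, 0.2, 0.26, 0.3, 0.4 and 0.5. With 56 or 62 points the results are within about 3 percentage points. Half of the mismatches run each way, so a response seems gained in at most about 25% and lost in at most about 25%.

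**All 29 lags at p < 0.05.** With r = 0 and independent lags, one lag disagrees with probability 2 × 0.05 × 0.95 = 0.095, so at least one disagrees with probability 1 − 0.905^29 = 94%. In simulation, where lags share data, the set of significant lags differed in roughly 86–93% of unchanged patients over r = 0 to 0.5.

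**Correcting over lags does not cure it.** With a Bonferroni threshold over 29 lags, the set still differed in 31% at r = 0.3 and 51% at r = 0.4.

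**A direct test of the difference.** Dividing the difference of the two Fisher z values by √(2/57) = 0.187 rejects in about 4–5% of unchanged patients across the range of r. Its simulated power with 60 points per month is 39% for a fall in r from 0.4 to 0.1, 60% for 0.4 to 0, and 82% for 0.5 to 0. The difference detectable with 80% power is (1.96 + 0.84) × 0.187 = 0.52 on the z scale.

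**The case against.** The strongest reply is that the faulty rule appears nowhere in the article. The cross-correlation test is given a narrower purpose, lead and lag between variables, and is a legitimate method for that. This stands. A reader might infer that the plan will call a response changed when it is significant in one month only, and hence that up to half of the patients will be misread. The documents support neither. The rule is an assumption made for the calculation, and one half is the worst case for one lag at an assumed correlation. For the same reason it cannot be said that the reported changes will be mostly noise.

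A second reply is that a journal article may leave the contrast to the full protocol or to the cited design paper. This stands in part: if a contrast is specified there, only the article's wording needs to change. But the article is not silent. It fixes a method, a lag range and a significance level, and these address a different null hypothesis from its stated question. For the main trial the same section does name the matching contrast, the interaction of group and time.

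Third, a reader might infer that the control cases are not analysed. That goes too far: the analysis covers the single-case studies as a whole, so control cases are analysed within each month like the others. What is unstated is any comparison between the arms.

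Fourth, the component is exploratory, no efficacy conclusion rests on it, and one case had been conducted. This lowers the consequence. It does not turn a difference in significance into a test of change.

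Last, a difference at a fixed lag does not capture a change in the shape or delay of a response. That is fair, and is a reason to allow a model-based contrast over a lag window.

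**Conclusion.** The point holds as a mismatch between question and test. The single-case question is a before-to-after change credited to the programme; the stated analysis tests dependency within one month, and no contrast between periods or between arms is given. The mismatch is in the text and rests on no numerical assumption.

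The error rates are conditional on the reading rule and inputs listed in the working. They show what the only significance-based route that the section offers would produce, not what the investigators have said they will do.

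Severity is low to moderate, because the work is exploratory and few cases may accrue.

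**What to change.** In the single-case part of Statistical analyses, for the before–after question:

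- Add a direct per-patient contrast at pre-chosen variable pairs and lags: the Fisher z difference between the two months' residual cross-correlations, or a period-by-predictor interaction in the planned VAR or a transfer-function model fitted to both months. Report it with a 95% confidence interval.
- Keep the tests against zero as a description of each month, and state that a difference in significance between months is not evidence of change.
- Set the changes in intervention cases beside those in control cases descriptively, with a permutation test only if enough cases accrue. Otherwise do not attribute a change to the programme.

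The cost is a few sentences and a few lines of R on data already planned; since further cases are being sought, the change can still take effect. The drawback is sensitivity: with power of about 39–82% even for large changes in one patient, fewer changes will be declared, and the results must stay exploratory.

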## Discussion

RA has numerous implications. It affects individuals, causing chronic pain, fatigue, insomnia, and limitations in performing daily activities. At the public health level, it generates a population of patients with lasting disabilities who require long-term therapy. This study adopts a holistic treatment approach that integrates various disease aspects, considering their interactive relations in accordance with the biopsychosocial model [47]. RA has been demonstrated to impact not only physiological and psychological outcomes but also to emerge or worsen due to psychophysiological mechanisms triggered by psychosocial stressors. A combination of different treatment modalities may prove more efficient over time at the individual and public health levels by improving the RA disease activity of the patients, increasing their quality of life and reducing treatment expenditures.

Methodologically, the proposed PNI project consists of a combination of two main study approaches, which both integrate biopsychosocial datasets collected over time with temporal data analyses, allowing a comprehensive analysis of within- and between-subject effects. This represents an expansion and innovation compared with the usual RCT approach to the topic under study [3]. Especially with our second approach, integrative single-case studies, it becomes possible to move beyond simply determining a treatment effect achieved by pooling data across participants and instead examine *interindividual* variation. Rather, this approach takes a “microscopic” perspective by analysing the *intraindividual* variation of real-life biological, psychological, and social data over time, thereby investigating under the highest possible ecologically valid conditions (“life as it is lived”) *how* an intervention changes the functional characteristics of the stress system in individuals with RA.

This study has all of the usual limitations inherent to any study with a limited sample size and data acquired in a limited region and period in terms of generalizability. In addition, other biases could emerge from patients’ voluntary and self-motivated participation after receiving information about the study goals, which could selectively favour the enrolment of patients who are receptive to psychological intervention. Furthermore, this study aims to evaluate the benefits of the psychological intervention as an addition to treatment-as-usual with a waiting-list control. Therefore, it will only provide limited insights into the mechanisms of effects that could be tested with additional (active) control groups.

The proposed study is clinically and methodologically in line with the biopsychosocial model [47, 48], a paradigm in medicine that focuses on the complex and thereby individual aspects of human life. In this regard, personalized and individual health literacy concepts represent an innovation that promotes individual health and life skills, enables patients to experience self-efficacy, and effectively strengthens their self-management. Improving health literacy among groups incurring high healthcare costs will yield significant benefits for both the affected individuals and the healthcare systems.

We plan to disseminate the study results in relevant peer-reviewed journals and conferences. The decision-making authority on publishing details lies within the project’s consortium. Furthermore, to provide flexible answers to research questions and follow-up investigations, a second dataset that does not include any patient-identifying variables or routine data from the health insurance companies will be created in addition to the primary dataset. As a result, the dataset will be completely anonymized and can be forwarded for the purposes mentioned above.

## Trial status

(Protocol version 5.0, 24th October 2023)

Recruiting started on 1st February 2022 and ended on 30th September 2023. The study successfully enrolled a total of 73 individuals, with 34 participants in the control group (2 withdrawals) and 39 participants in the intervention group (8 withdrawals). As of now, one integrative single-case study has been conducted. Additional integrative single-case studies are pursued.

## Data Availability

The datasets analysed during the current study and the statistical code are available from the corresponding author upon a reasonable request, as is the full protocol. The participant informational materials and informed consent form are available from the corresponding author upon request.

## Abbreviations

RA: Rheumatoid arthritis
EULAR: European League Against Rheumatism
BKK-LV Bayern: Betriebskrankenkassen Landesverband Bayern (Bavarian Association of Company Health Insurance Funds)
AOK Bayern: Allgemeine Ortskrankenkasse Bayern (General Local Health Insurance Fund Bavaria)
DPtV Landesgruppe Bayern: Deutsche PsychotherapeutenVereinigung Landesgruppe Bayern (Bavarian regional group of the German Psychotherapists Association)
BDRh: Berufsverband Deutscher Rheumatologen (Professional Association of German Rheumatologists)
KVB: Kassenärztliche Vereinigung Bayerns (Bavarian Association of Statutory Health Insurance Physicians)
UR: Universität Regensburg (University of Regensburg)
MUI: Medizinische Universität Innsbruck (Medical University of Innsbruck)
G-BA: Gemeinsamer Bundesausschuss (Innovation Committee at the Federal Joint Committee)
BLÄK: Bayerische Landesärztekammer (Bavarian Medical Association)
ICD-10: International Statistical Classification of Diseases and Related Health Problems
GLK: Gesundheits- und Lebenskompetenz Training
HEDE: Health-Ease and Dis-Ease
HGT: Hildesheimer Gesundheitstraining
ZRM: Zürcher Ressourcen Modell
STAXI-2: State-Trait Anger Expression Inventory-2
TAS-26: Toronto Alexithymia Scale
SF-12: 12-Item Short Form Survey
heiQ: Health Education Impact Questionnaire
PSQI: Pittsburgh Sleep Quality Index
PHQ-9: Depression Module of the Patient Health Questionnaire
DSM-IV: Diagnostic and Statistical Manual of Mental Disorders
NEO-FFI: NEO Five-Factor Inventory
TNF-α: Tumour necrosis factor α
IL-1β: Interleukin-1β
IL-2: Interleukin-2
IL-2R: Interleukin-2 receptor
IL-6: Interleukin-6
IL-10: Interleukin-10
IL-12: Interleukin-12
IL-13: Interleukin-13
CRP: C-reactive protein
ESR: Erythrocyte sedimentation rate
ACPA: Anti-citrullinated protein antibody
DAS 28: Disease Activity Score 28
SDAI: Simplified Disease Activity Index
CDAI: Clinical Disease Activity Index
FFbH: Funktionsfragebogen Hannover (Hannover Functional Ability Questionnaire)
VAS: Visual analogue scale
cs/tsDMARD: Conventional synthetic or targeted synthetic disease-modifying antirheumatic drugs
b/bsDMARD: Biological or biosimilar disease-modifying antirheumatic drugs
Na-EDTA: Sodium ethylenediaminetetraacetate
SCID-5: Structured Clinical Interview for DSM-5
LEDS: Life Events and Difficulties Schedule
OPD: Operationalized Psychodynamic Diagnosis
DIARI: Daily Inventory of Activity, Routine and Illness
IHI: Incidents and Hassles Inventory
BMI: Body mass index
ARIMA: Autoregressive integrated moving-average model
VAR: Vector autoregressive model
